## Abstract

**Background:**

Management of acute sore throat poses a significant burden on UK general practices, with almost 10% of registered patients attending their GP with sore throat every year. Nearly half of all patients presenting with acute sore throat are treated with antibiotics, despite their limited effect. In a recent systematic review we demonstrated that a single dose of steroids reduced the severity and time to resolution of sore throat. However, all of the trials included looked at the use of steroids alongside antibiotics and only one was in a primary care setting. This trial aims to assess the efficacy and cost-effectiveness of a single oral dose of corticosteroids on symptoms of sore throat in patients receiving either a delayed antibiotic prescription or no antibiotics at all in UK primary care.

**Methods/Design:**

A double-blind, two arm, randomized, placebo controlled trial in adults (≥18 years of age) presenting to primary care with acute sore throat (<seven days). Participants are recruited on the day of presentation to their GP practice. GPs or nurses assess eligibility, record baseline clinical features and obtain a throat swab for bacterial culture. Participants are being randomized to treatment arms at a ratio of 1:1. Treatment arms will be stratified according to whether patients are being given a delayed antibiotic prescription or no antibiotic prescription and by recruiting centre (Oxford, Bristol or Southampton). Outcome data is being collected at 24 and 48 hours via text message or telephone call, from days 0 to 7 using a patient symptom diary and at one month via a GP notes review.

**Discussion:**

This will be the first randomized controlled trial of oral corticosteroids in adults presenting to primary care with sore throat in the UK, and the first to examine the clinical and cost-effectiveness of oral corticosteroids for the treatment of sore throat in the absence of antibiotics.

**Trial registration:**

This trial is registered with Current Controlled Trials on 26 March 2013, registration number: ISRCTN17435450.

**Electronic supplementary material:**

The online version of this article (doi:10.1186/1745-6215-15-365) contains supplementary material, which is available to authorized users.

## Background

### Epidemiology, costs and current management of sore throat

Sore throat is a common complaint and is a frequent reason for patients to attend primary care. In 2006, nine patients consulted a general practitioner (GP) with sore throat for every 100 patients registered [1]. Tonsillitis was diagnosed in 3 out of 100 patients registered, and of these, 91% received antibiotics. Half of the remaining cases, coded as sore throat or pharyngitis, also received antibiotics. Prescribing rates for sore throat are clearly disproportionately high, especially since treatment of sore throat with antibiotics provides only modest symptomatic benefit [2, 3].

Antibiotic resistance in general is still increasing across Europe and represents a growing threat to the effectiveness of antibiotics [4–6]. Although prescribing rates have fallen for patients presenting with the common cold, a similar decrease has not been noted for sore throat [1]. Part of the reason may be the absence of alternative symptomatic treatments, resulting in a prescribing ‘vacuum’.

The lost productivity associated with tonsillitis has been estimated at £190 per episode [7]. The weekly UK incidence of patients presenting to their GP with sore throat averages at 60 per 100,000 in the current population. Extrapolating from this, we might expect a cost of almost £6 per person per year in lost productivity alone (equating to £370 million at 2010 population figures), in addition to an estimated £60 million cost in GP consultations [8].

### Rationale for testing the effectiveness of corticosteroids in sore throat

Corticosteroids may offer an alternative symptomatic treatment for sore throat. They are known to inhibit transcription of the pro-inflammatory mediators in airway endothelial cells which are responsible for pharyngeal inflammation and ultimately symptoms of pain [9]. Steroids are beneficial in other upper respiratory tract infections such as acute sinusitis, croup, and infectious mononucleosis [10–13]. Short courses of even high-dose oral steroids are considered to be safe, in the absence of any specific contraindications [14].

A systematic review and meta-analysis of randomized controlled trials assessing the benefit of oral corticosteroids in sore throat [15, 16] identified eight eligible trials. The review found that a single dose of oral or intramuscular dexamethasone increased the likelihood of complete resolution of pain at 24 hours by more than three times (relative risk 3.2 (95% CI 2.0 to 5.1; *P* <0.001), absolute risk reduction 27% (95% CI 17 to 36%), number needed to treat 3.7 (95% CI 2.8 to 5.9)). The mean time to onset of pain relief was reduced by more than 6 hours (95% CI 3.4 to 9.3; *P* <0.001). However, all of the included trials compared steroids to placebo in addition to oral antibiotics. Furthermore, only one of the trials (in Israel) recruited patients presenting to primary care. We have searched the International Controlled Trials Register to confirm there are no similar trials currently being conducted or registered.

### Justification for treatment dose and method

The dose of oral corticosteroid used in the majority of previous trials in adults was a single dose of 10 mg of dexamethasone or the equivalent dose of prednisolone, either orally, or intramuscularly, or both. Those trials included children up to the age of 18-years-old and used 10 mg of dexamethasone as the maximum dose. Our systematic review found no difference in the effect of oral compared to intramuscular administration of corticosteroid. Therefore this trial is using a single dose of 10 mg of oral dexamethasone as the dose most commonly found to be effective and the treatment method causing the least discomfort.

### Known and potential risks to human participants

Long-term steroid use is known to be associated with an array of systemic side effects [17]. However, in the absence of specific contraindications [17, 18], a short (up to 1 week) course of high-dose steroids is considered to be safe and associated with few side effects [19]. Our systematic review found no difference in either serious adverse events or all adverse events, relapse or recurrence rates between participants receiving corticosteroids and those receiving placebo [15].

The prospect of achieving rapid symptomatic relief with a single dose of oral steroids has positive implications: improving patient treatment options, reducing unnecessary antibiotic prescriptions and reducing the economic burden of sore throat. However, evidence is required for the clinical and cost-effectiveness of oral steroids in sore throat in the absence of antibiotics and in a primary care population. We are therefore conducting a randomized double-blind trial comparing a single dose of oral dexamethasone to placebo in adults aged 18 years or over presenting to UK primary care (Treatment Options without Antibiotics for Sore Throat or TOAST trial).

## Methods/Design

### Objectives

The primary objective of the trial is to investigate if, in adults ≥18 years presenting to primary care with acute sore throat, the use of a single dose of oral dexamethasone leads to increased speed of resolution or improvement in symptoms compared with placebo.

The trial has several secondary objectives. Firstly, to investigate whether dexamethasone compared with placebo leads to increased resolution or improvement in symptoms in those patients who have not been prescribed antibiotics. Secondly, to investigate whether dexamethasone compared to placebo will, in those patients offered a delayed antibiotic prescription, reduce the number of patients taking antibiotics for their sore throat within seven days. Thirdly, to investigate whether a single dose of oral dexamethasone compared to placebo will: reduce time away from work or education within seven days, not increase the incidence of hospital admission with complications related to sore throat (such as peritonsillar abscess) within 28 days, not increase repeat attendance at the GP within 28 days with symptoms or complications of sore throat, and be cost-effective. Fourthly, to assess predictors of response to corticosteroids including existing severity scores (FeverPAIN score and Centor score), baseline factors and positive bacterial throat swab.

### Trial design

The trial is a two arm, individually randomized, double-blind trial comparing a single dose of 10 mg oral dexamethasone with placebo in adults aged 18 years or over presenting to primary care with sore throat. The trial requires a single visit to the GP from each participant and a one-week period of participant involvement from the point of randomization and treatment. See flow chart (Additional file 1). The trial will be a multicenter trial based at general practices in Oxford, Bristol and Southampton in England, UK.

### Primary and secondary endpoints and outcome measures

#### Primary outcome

The primary outcome of this trial is the direct report by the patient of presence or absence of complete resolution of sore throat at 24 hours by either text message or telephone.

#### Secondary outcomes

The trial has several secondary outcomes which include: direct report by those patients who have not been prescribed antibiotics of presence or absence of complete resolution of sore throat at 24 hours by either text message or telephone, and report of presence or absence of complete resolution of sore throat at 48 hours by either text message or telephone contact. Additionally we will record for the seven days after treatment is administered: time to onset of pain relief (in hours), time to complete symptom resolution (in hours), report of difficulty swallowing and pain on swallowing, the duration of moderately bad symptoms recorded by validated symptom diary, the change in ratings of sore throat pain and pain on swallowing by visual analogue scale, the uptake of delayed antibiotic prescription and any time missed from work or education.

Furthermore we will record the severity of symptoms in the two to four days after seeing a GP based on the symptom diary, any attendance at GP practices, Emergency Departments, or out-of-hours centers within 28 days with symptoms or complications associated with sore throat such as peritonsillar abscess, any hospital admission with related complications of sore throat within 28 days, use of over-the-counter medications and prescription medications (including, if delayed antibiotics are taken, whether the course is completed and whether any other antibiotics were taken) in the first seven days and cost-effectiveness measures which include incremental cost, EuroQol EQ-5D-5L score change in seven days and impact on usual activities over most recent seven days

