#### Screening and eligibility assessment

The primary care site gives adults presenting with sore throat a participant information sheet which details what is involved in trial participation. During the initial consultation the primary care clinician (referred to from now onwards as the responsible clinician) discusses trial participation and screens the participant using the inclusion and exclusion criteria. The responsible clinician may be a triage nurse if the GP judges that they are competent to perform the baseline assessment and eligibility screening. Any patient who is not eligible to participate or declines to participate will be recorded on the screening log with reasons for ineligibility or declining (if known) and have no further involvement in the trial.

The responsible clinician completes their routine clinical management, and at the clinician’s discretion will offer a delayed antibiotic prescription, to be collected by the patient either from the recruiting clinician at their subsequent baseline trial assessment, or from the reception of the GP practice according to the standard procedure of the practice. The delayed antibiotic prescription will be accompanied by: reassurance that antibiotics are often not needed immediately and information about the disadvantages of antibiotics, information about the natural history of sore throat and advice to use regular pain relief, instructions for the antibiotics to be collected and used after three to five days if the patient feels their symptoms are not starting to improve, or sooner if their symptoms are getting significantly worse and a brief information leaflet containing instructions and explanation regarding a delayed prescription to reinforce these points.

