#### Subsequent assessments

Following the baseline trial assessment participants complete a symptom diary reporting upon the resolution of symptoms and time to onset of pain relief, and rating their pain on a visual analogue scale every day for seven days on paper. As well as recording the severity and duration of their symptoms, this also includes providing information about NHS resource use, out-of-pocket expenditure, use of over-the-counter and prescription medications and time off work and/or education or foregone leisure time. Within the symptom diary we also ask participants to complete the EuroQol EQ-5D-5L instrument [20] daily for seven days following study entry.

Participants are telephoned or texted at 24 and 48 hours to support collection of the primary outcome and secondary outcomes. As preference this contact will be made via text message because of the greater accuracy with times and standardization. They are additionally telephoned in the first 96 hours if required to support and encourage completion of the symptom diary; they will also receive a text message at day four and day nine to encourage completion of the symptom diary and to remind them to return it to the PC-CTU. Follow-up is being undertaken by research coordinators at all three centers. Follow-up continues for seven days from the initial day of recruitment. Participants are asked to report in the diary any use of medications, including whether they obtained and completed the delayed antibiotic prescription. If participants do not complete the symptom diary over the seven days we send them a short questionnaire after this in order to collect information for key secondary outcomes relating to the first four days after taking the trial medication and, if needed, they are telephoned in order to help them complete the questionnaire. All paper diaries and questionnaires are sent back to the respective centre in pre-paid envelopes.

A review of the primary care notes is undertaken by the recruiting primary care site one month post-randomization, to record repeat presentation to a GP, Emergency Department or out–of-hours primary care centre with symptoms or complications of sore throat, hospital admissions and use of prescription medications. Baseline information about past medical history and acute and repeat medication usage is also collected.

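### Completion of a delayed antibiotic course is scored within seven days, but a course of six days or more started when advised cannot finish in that window

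*Protocol article*

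**What the plan says.** All of the statements below are in the protocol article.

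- **Outcome and window.** Secondary outcomes lists over-the-counter and prescription medication use, with the sub-item "if delayed antibiotics are taken, whether the course is completed and whether any other antibiotics were taken) in the first seven days".
- **Start advice.** Screening and eligibility assessment says the delayed prescription comes with "instructions for the antibiotics to be collected and used after three to five days if the patient feels their symptoms are not starting to improve", and continues "or sooner if their symptoms are getting significantly worse".
- **Source of the item.** Subsequent assessments has participants report medication use in the diary, "including whether they obtained and completed the delayed antibiotic prescription". The abstract describes outcome collection "from days 0 to 7 using a patient symptom diary".
- **End of participant follow-up.** Subsequent assessments: "Follow-up continues for seven days from the initial day of recruitment".
- **Fallback.** A participant who does not complete the diary is sent a short questionnaire on key secondary outcomes "relating to the first four days after taking the trial medication".
- **Later contacts.** A day-nine text encourages diary completion and return. A notes review at one month covers, among other things, prescription medication use. Neither is described as asking whether a course was finished.
- **Course length.** None is stated. Baseline assessments records the prescribed duration for each patient.
- **Analysis.** Statistical analysis for effectiveness and safety names uptake of the delayed prescription within seven days. It names no analysis of completion.

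**The concern.** The outcome window, the advised start and the end of follow-up do not fit together for longer courses. A patient who starts on day 4 or 5 and takes every dose may still be mid-course when follow-up closes. Read literally, the outcome then puts that patient with those who gave up early.

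The resulting misclassification need not be balanced between arms. The start advice depends on symptoms, and the trial tests whether dexamethasone improves symptoms. If dexamethasone shifts start days later, fewer courses in that arm would be complete by day 7 even with identical adherence. A reader of a completion table by arm could mistake this for a difference in adherence or in the amount of antibiotic taken. If completion is not asked after day 7 and antibiotic use is not dated, no later analysis can recover the distinction.

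**Working it through.** The plan gives no figure for completion, so there is nothing to reproduce. The check is a day count.

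**Inputs**
- Day 0 is the day of recruitment and observed dosing. The baseline assessment takes place within six hours of the consultation, so the start advice runs from the same day (Baseline assessments).
- Advised start day s = 3, 4 or 5, reading the advice as study days; earlier if significantly worse (Screening and eligibility assessment).
- Last day of diary and participant follow-up = 7 (abstract; Subsequent assessments).
- Course length L is not given. It is an assumption here, run from 1 to 10 days.

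**Formulas**
- Start day counted as the first course day: the last course day is s + L − 1, so completion by day 7 needs L ≤ 8 − s.
- Stricter count on elapsed days: s + L ≤ 7, so L ≤ 7 − s.

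**Longest course that can finish by day 7**
- s = 3: 8 − 3 = 5 days (elapsed: 4)
- s = 4: 8 − 4 = 4 days (elapsed: 3)
- s = 5: 8 − 5 = 3 days (elapsed: 2)

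**Advised start days (3, 4, 5) that allow completion, by course length**

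| Course length | Start day counted | Elapsed days |
|---|---|---|
| 2 days or less | 3 of 3 | 3 of 3 |
| 3 days | 3 of 3 | 2 of 3 |
| 4 days | 2 of 3 | 1 of 3 |
| 5 days | 1 of 3 | 0 of 3 |
| 6 days or more | 0 of 3 | 0 of 3 |

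**Early starts.** The latest start that allows completion is 8 − L (elapsed: 7 − L). A 5-day course needs a start by day 3 (elapsed: day 2), and a 7-day course by day 1 (elapsed: day 0). For a 10-day course the result is negative (8 − 10 = −2), so it cannot finish inside follow-up whenever it is started.

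**Sensitivity to start day.** Take a 5-day course, full adherence and the start day counted. A start on day 3 ends on day 3 + 5 − 1 = 7 and counts as complete. A start on day 4 ends on day 8 and does not. One day's difference in start reverses the classification with no difference in adherence.

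**If the diary were filled in as late as day 9**, when the last text is sent, the limit becomes L ≤ 10 − s, that is 7, 6 or 5 days for starts on day 3, 4 or 5. This eases the problem without removing it, and the answer would no longer describe the first seven days.

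**The case against.** The strongest reply is that much depends on things the article does not show.

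- **Course length.** A reader might infer that most delayed courses cannot be finished in the window. The article does not support that: it states no length, and courses of 2 days or less started as advised finish on either count. The point holds only conditionally on length.
- **Early starts.** The advice allows a sooner start on significant worsening, and some of those courses could finish. Their share is unknown, so no overall proportion of affected courses can be given.
- **Diary format.** A reader might infer that an adherent patient must report non-completion on day 7, or that the item captures only start date. The diary is not shown and may offer a still-taking answer or date antibiotic use, and the day-nine text still encourages its completion. Short or early courses can be classified correctly in any case.
- **Later use.** It would be wrong to say that all antibiotic information after day 7 is lost. The notes review covers prescription medication use to one month, though it is not described as recording whether a course was finished.
- **Weight.** Completion is a parenthetical sub-item with no named comparison. The stated antibiotic objective and the analysed outcome are uptake within seven days.

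These points stand and limit the finding. They do not remove it. The outcome, its window, the start advice and the end of follow-up are all stated in the article, and for longer courses they conflict. This is therefore not a detail merely left to the analysis plan. The one fallback described makes matters worse, since the short questionnaire concerns the first four days.

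**Conclusion.** The point holds in conditional form. For any course of 6 days or more started when advised, completion within the stated window is impossible on either day count. For a 5-day course it is possible only with a start by day 3 (start day counted) or day 2 (elapsed days). For these courses the item as defined cannot separate early stopping from treatment still running at day 7, and its value depends on start day, which dexamethasone may influence. Such an influence is plausible from the symptom-based start advice, but no figure in the article measures it.

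The conclusion assumes that day 0 is the day of recruitment and that completion is judged at day 7, as the outcome states. How many participants are affected depends on prescribed durations and start days that the article does not give.

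The weight is small. The primary outcome, the sample size and uptake of antibiotics within seven days are unaffected, and the article does not support reading this as a bias in the trial's antibiotic-use result. It is a cheap improvement worth making.

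**What to change.** Replace completion in the first seven days with two recorded quantities for each participant who starts antibiotics: the start day and the number of antibiotic days taken by day 7. Read these against the prescribed duration already collected at baseline, and classify each course as completed, stopped early or still running at day 7.

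If the diary does not date antibiotic use, add that item. Alternatively, keep completion as the outcome and put the question, in a later text to those who reported starting, after their last prescribed day.

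The cost is a small change to the outcome definition and its derivation, plus possibly one diary or text item. If the diary already dates antibiotic use, no new participant contact is needed. The advice to patients on when to start antibiotics is not to be changed; only the measurement is.

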### Inclusion criteria

Trial participants will be anyone aged 18 years or over presenting to primary care with acute sore throat which is judged by the clinician to be infective in origin, whose onset of symptoms has been within seven days of presentation and has the capacity and willingness to complete trial documentation.

